##### Clinical outcomes

Development of clinical outcomes related to lifestyles including general obesity, central obesity, hypertension, diabetes mellitus, dyslipidemia, sarcopenia, arteriosclerosis, osteoporosis, and fatty liver, will be compared with past medical history supplemented by physical examination and laboratory test indicators. Venous blood samples, collected after overnight fasting (at least 8 h), will be used for clinical laboratory testing, including routine blood tests, fasting blood glucose, lipid levels and hepatic function. If local clinical centers are not equipped with relevant testing devices, uniform devices will be provided and doctors and nurses will be trained to operate these devices, including bone mineral density densitometers (OSTEOKJ3000) among others. All procedures for clinical examinations will be in line with the standard operating procedures (SOPs) of the CMEC as documented elsewhere [33].

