### Timeline of data collection

Participants who meet the inclusion criteria will undergo baseline data collection given informed consent. Communities will only be randomized after this baseline data collection, with corresponding allocation of participants to experimental or control group. Demographic characteristics and medical records data will respectively be surveyed and extracted at baseline. Primary outcome and secondary outcomes assessed with questionnaires and scales will be collected at five measurement points: baseline, 3 months after baseline, primary end-point. That is end of instructed intervention period (6-month follow-up), 9-month follow-up, and 12-month follow-up. Laboratory data will be collected at four time points: baseline, 3 months, primary end-point (6-month), and 12-month follow-up (Fig. 3).

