**Fig. 3 Fig3:**
[figure not shown]
SPIRIT flow diagram for the schedule of enrolment, interventions, and assessments. FFQ, Food Frequency Questionnaire; IPAQ, short version of the International Physical Activity Questionnaire; PSQI, Pittsburgh Sleep Quality Index; GAD-7, 7-item scale for General Anxiety Disorder; PHQ-9, patient health questionnaire depression module; mGSES, modified General Self-Efficacy Scale; MoCA-B, Montreal Cognitive Assessment, Basic Version; mMSPSS, modified Multidimensional Scale of Perceived Social Support; SPPB: Short Physical Performance Battery; PWV, pulse wave velocity; QCT: Quantitative Computed Tomography; BMD: bone mineral density; CTA: computed tomography angiography. ^a^Blinding of participants, assessors, and statisticians. ^b^Body circumference included neck, waist, belly, hip, arm and leg circumference. ^c^SPPB included feet together test, semi-tandem stand test, tandem stand test, 4-m walk test, and five times sit-to-stand test. ^d^Color doppler ultrasonography included abdominal, carotid and cardiac ultrasonography. ^e^Blood tests include total white blood cell count (WBC), red blood cells (RBC), haemoglobin (HGB), platelets (PLT), lymphocytes, monocytes, neutrophils, eosinophils, fasting blood glucose fasting blood glucose (FBG), triglycerides (TG), cholesterol (CHOL), high-density lipoprotein cholesterol (HDL-CH) and low-density lipoprotein cholesterol (LDL-CH), total protein (TP), albumin, globulin, alanine transaminase (ALT), aspartate amino transferase (AST), gamma-glutamyl transpeptidase (GGT), Creatinine (Cr), urea, uric acid (UA) and C-reactive protein (CRP). ^f^Including metagenomics and metabolomics. X The item will be surveyed implemented or on relevant time point.

The item will be implemented in the relevant time period.

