### Harms

An adverse event is defined as any unfavorable medical event that occurs after a subject has received an intervention, but is not necessarily related to the intervention. If the current state of the study subject is a pre-existing condition known from medical history, it should not be considered an adverse event unless there is a change in nature, severity, and association. Although the intervention is non-invasive, participants will be asked to inform research assistants as soon as they experience symptoms of discomfort. Any adverse events will be documented as to the nature of the event, time of occurrence, etc., and will be followed up until medically resolved. This study does not involve invasive manipulation or medication, and adverse events expected to occur may be related to the study participant's own illness or the trial. In the course of the trial, in the event of a serious adverse event, the first relevant treatment should be carried out immediately so that the impact of the adverse event on the study subject is minimized; if the interests of the patient conflict with the testing process, the interests of the patient are prioritized, and the trial is terminated if necessary. Study subjects may discontinue or withdraw from the trial at any time or report to the research team. Research assistant will keep a detailed record of all adverse events during the trial, including time, symptoms, and treatment, and report them to the Supervisory Group, the Ethics Committee, and the study sponsor.

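### The Harms section says nothing invasive is done and counts adverse events only from the intervention onward, so an event from the baseline blood draw falls outside the definition

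*Protocol article*

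**What the plan says.** In the protocol article, the Harms section describes the study as a whole in these words: "This study does not involve invasive manipulation or medication". A little earlier the same section speaks of the intervention alone: "Although the intervention is non-invasive, participants will be asked to inform research assistants as soon as they experience symptoms of discomfort". It sets the start of the safety window as follows: "An adverse event is defined as any unfavorable medical event that occurs after a subject has received an intervention". It adds that no link to the intervention is needed for an event to count. Research assistants are to record adverse events and report them to the supervisory group, the ethics committee and the sponsor.

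The Clinical outcomes section plans blood sampling: "Venous blood samples, collected after overnight fasting (at least 8 h), will be used for clinical laboratory testing". The Timeline of data collection schedules laboratory data at four points: baseline, 3, 6 and 12 months. It also fixes the order of events: "Communities will only be randomized after this baseline data collection". The section on randomization and allocation concealment gives the same order.

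The legend of Fig. 3, the schedule of assessments, expands further abbreviations: "QCT: Quantitative Computed Tomography; BMD: bone mineral density; CTA: computed tomography angiography". The body of that figure is not available here.

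**The concern.** There are two separate problems.

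The first is a mismatch. Drawing venous blood is an invasive procedure, if a minor one. A sentence saying that the study involves nothing invasive is therefore wrong as written.

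The second is a gap in a stated safety rule. The window opens when a participant has received an intervention, but the baseline assessment, with its overnight fast and blood draw, takes place before allocation. A faint after fasting, or a nerve or vessel injury from that draw, would come from something the study asked of the participant. It would still not meet the study's definition of an adverse event. Because the recording and reporting duty is written for adverse events, staff who follow the rule would have no obligation under it to record such an event or pass it on to the bodies named in the Harms section.

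What is at stake is complete safety reporting. No endpoint, power figure or efficacy analysis is affected.

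**Working it through.** The plan gives no figure to reproduce. The check sets the sections side by side, with one count for scale.

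**Step 1: scope of the no-invasive-procedures sentence.** Its grammatical subject is the study. The Harms section has already called the intervention non-invasive in another sentence, so the later one reads most naturally as the wider statement. Read that way, it conflicts with the venous sampling in Clinical outcomes. Read as referring to the intervention only, it is accurate.

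**Step 2: order of events.**
- Consent, then baseline data collection, including laboratory data (Timeline of data collection).
- Randomization of communities (same section, and Randomization and allocation concealment).
- Start of the active or placebo intervention. Both arms receive something, so the adverse-event window opens in both, but not before this step.
- Laboratory data at 3, 6 and 12 months.

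The baseline draw precedes the opening of the window and the other three draws follow it. Since the definition needs no causal link to the intervention, any event from a draw at 3, 6 or 12 months counts.

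**Step 3: does another section close the gap?** Data monitoring provides for systematic checks of negative events and a meeting after each assessment point. Quality control plans forms for monitoring safety. The ethics section mentions injury related to the study. None of these alters the definition in Harms or attaches the reporting duty to events outside it.

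**Step 4: scale.** Inputs are 256 participants (Sample size), four laboratory time points (Timeline of data collection) and, as an assumption, one draw per participant per time point.
- Planned samplings at full attendance: 256 × 4 = 1,024.
- Before the window opens: 256 × 1 = 256.
- Share: 256 / 1,024 = 25%.

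Dropout raises the share. As an extreme case, suppose all the planned attrition occurs before the 3-month visit, leaving the 204 participants the sample size section requires. Samplings are then 256 + 3 × 204 = 868, and the share is 256 / 868 = 29.5%. The range is therefore about 25% to 29.5% of draws. The documents give no event rate, so the number of missed events cannot be estimated.

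**The case against.** The best defence is that the sentence is loose wording. It follows soon after the remark that the intervention is non-invasive and is paired with medication, so it may mean only that no invasive or drug treatment is being tested. That reading is possible, and one qualifier would make it explicit. It does not touch the definition of an adverse event.

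Starting the window at the intervention can also be defended as a design choice. Events before randomization cannot bias the comparison between arms, and general oversight is in place. Both observations are correct. They justify keeping baseline events out of the comparison, but not leaving events caused by the study's own procedures outside the recording rule.

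A reader might be tempted to go further, in four ways that the documents do not support:
- **CT as the main hazard.** CT angiography and quantitative CT appear only as abbreviations in the Fig. 3 legend. The text does not say when, in whom or how often they are done, and it does not mention injected contrast. Quantitative CT is not in itself invasive. Whether any scan falls at baseline cannot be established.
- **Assessment procedures as the main physical risk of the trial.** No event rates are given for either the procedures or the intervention, so this cannot be ranked.
- **A faulty consent form.** The form is not shown. The ethics section says it explains potential risks, and nothing indicates that sampling is left out.
- **Later procedure-related events also missed.** They are covered. The definition requires no causal link, and the Harms section itself foresees events related to the trial.

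**Conclusion.** The point holds in a limited form and is minor. The Harms section conflicts with the planned venous sampling unless its sentence is restricted to the intervention. Its adverse-event definition also excludes events from the baseline draw, which is one in four planned samplings at full attendance. That proportion describes draws, not harm.

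The conclusion rests on the article as the statement of the safety rule, on one draw per participant at each listed laboratory time point, and on baseline sampling being done before allocation as the timeline says. For the CT procedures the same gap would arise only if Fig. 3 schedules them at baseline, which cannot be seen here.

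**What to change.** Reconcile the Harms section with Clinical outcomes, Timeline of data collection and Fig. 3:

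1. Limit the sentence on invasive manipulation and medication to the intervention.
2. Name the study's own assessment procedures as possible sources of events: venous sampling after fasting, and any CT procedure that Fig. 3 actually schedules. Which procedures are done, and in whom, is for the investigators to settle.
3. Start adverse-event recording at consent or at the first study procedure, identically for participants of both arms.
4. Record relatedness to study procedures separately from relatedness to the intervention.
5. Report events before randomization in their own table, apart from the between-arm comparison.

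The cost is revised wording in the protocol and an additional item on the adverse-event form. A few more events will be recorded before randomization. No extra visits or staff are needed, and the efficacy analysis does not change.

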### Quality control and quality assurance

All assessors will receive online training (videoconference) as regards the study protocol, including ethical norms and detailed instructions with respect to the evaluation process. Detailed description of assessment procedure will be provided in a standard operation manual. All group managers will receive unified training and learn about experimental and control group interventions before group assignment. Health professionals from local health community hospitals will help scheduling participants to take part in the program and resolve any issues that may arise during the implementation of the intervention.

During the intervention period, a monthly meeting will be held to review the current implementation of the program. Moreover, a series of forms will be designed to document implementation and monitor participants’ safety and compliance, including a form for participant risk grading, and a diary of participants’ adherence to the intervention, with which we will be able to identify individuals at risk and engage in timely activism to improve or enhance interventions.

Quality control (QC) for interviews using scales and questionnaires includes data quality control through inspectors, who will check for outliers and human error on the same day of data collection. QC for medical examination includes checking whether the measurement instruments were in good condition and inspecting whether the measurement was in accordance with standard operating procedures (SOPs). QC for clinical laboratory tests includes sending blind panels of samples to additional Third-Party Medical Laboratories for QC testing. As for QC for data entry, two independent assistants will check the data entered electronically against the trial record sheets. Any data identified as unqualified will be excluded from final analysis. All qualified data is stored on a dedicated data platform before analysis.

### Ethics approval, protocol amendments and consent

This trial will be conducted in compliance with the study protocol, the Declaration of Helsinki, and good clinical practice. Ethical approval for this study has been obtained from the Ethics Committee of the West China School of Public Health and West China Fourth Hospital (Gwll2022096).

The trial has been registered with the Chinese Clinical Trials Registry (ChiCTR2300070575, https://www.chictr.org.cn/index.aspx). The design and implementation of this cluster-RCT is in line with the extension of the SPIRIT 2013 statement [31], and reporting of the trial will be conducted according to the CONSORT statement [64].

Prior to participation, interested participants will be provided with a written informed consent form that includes details of the trial, an explanation of potential risks and benefits, and contact information for study members. Participants may choose not to participate in this study or request to withdraw from the study at any time by notifying the investigator, and any rights of the withdrawing person will not be affected as a result. The investigator may terminate a subject's continued participation in this study if the subject does not comply with the study plan, or if a study-related injury occurs.

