##### Termination criteria

Withdrawing informed consent and/or withdrawing from the trial;Development of new serious diseases that makes it inappropriate to continue the interventions as specified in the trial protocol;Experiencing serious adverse events during the intervention phase.

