### Data analysis

Data analyses will be performed using R version 4.2.1 for Windows. All data will be securely stored in an electronic database and accessible only to researchers who meet the criteria as provided in the research ethics approval document.

Descriptive statistics will be provided for the baseline sample. Categorical variables will be summarized in terms of frequencies and percentage, in total and by intervention group. Continues variables will be summarized as mean ± standard or median (interquartile range) in total and by intervention group.

All main analyses will be performed on intention to treat (ITT) basis. The primary outcome will be analyzed with mixed effects log-linear Poisson regression of any reduction of unhealthy lifestyles at six months (favorable outcome vs not) on intervention group as randomized at baseline [58]. In addition, the model will include a random intercept for subject nested in village and a fixed effect for town (as number of clusters not sufficient for variance estimation in the latter case). Treatment effect at six months (immediately after intervention) will be provided as relative risk ratio [59]. As regards secondary outcomes, reduction of unhealthy lifestyles (favorable outcome vs. not) at all timepoints will be simultaneously analyzed with longitudinal mixed effects log-linear Poisson regression on timepoint, and an interaction term of timepoint and intervention group, with random intercepts for subject nested in village and fixed effect for town as specified for the primary outcome. Other binary outcomes including smoking/drinking quitting, drug intake adherence, frailty will be analyzed in the same fashion. For continuous outcomes including sleep quality, smoking/drinking carving, mental health outcomes, cognitive function, self-efficacy, implicit health attitude, social support, longitudinal analysis of covariance (ANCOVA) models with time and time-group interaction will be estimated, adjusted for the respective outcome at baseline and featuring random intercepts for subject nested in village as well as a fixed effect for town [60]. Estimates of differences in changes in lifestyles between groups at 3, 6, 9, and 12 months will be analyzed post hoc using Wald-tests.

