#### Missing values

Attrition and dropout rates will be reported in terms of frequencies and percentages and patterns of missing data will be analyzed and respective tables and illustrations provided. Multiple imputation on 100 sets using chained equations with models according to variables’ scale levels will be performed for all main analyses [61].

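### The investigator may end study participation for non-compliance, and nothing keeps terminated participants in the 6-month assessment; this weakens the planned ITT analysis

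*Protocol article*

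**What the plan says.** Four parts of the protocol article bear on this.

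- **Ethics approval, protocol amendments and consent.** The investigator may end a subject's "continued participation in this study if the subject does not comply with the study plan"; an injury related to the study is a second ground. The rule is discretionary, applies to both arms, and concerns the study as a whole.
- **Termination criteria** (under Participants). Beside withdrawal of consent, the list has "Development of new serious diseases that makes it inappropriate to continue the interventions as specified in the trial protocol" and "Experiencing serious adverse events during the intervention phase". It does not say what is terminated, the intervention or the follow-up.
- **Data analysis.** "All main analyses will be performed on intention to treat (ITT) basis", and the primary model regresses the favourable outcome at six months "on intervention group as randomized at baseline".
- **Missing values and Sensitivity analysis.** The main analyses use "Multiple imputation on 100 sets using chained equations". Two sensitivity analyses are relevant: a per-protocol analysis with a 70% session threshold, and a reference-based imputation in which dropouts are assumed to follow the control pattern after leaving.

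The Timeline of data collection schedules assessments at baseline, 3, 6, 9 and 12 months. No section says whether a terminated participant is still invited to them.

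**The concern.** An intention-to-treat analysis needs the outcome of everyone randomised, whatever they did afterwards. A rule that ends study participation because of behaviour after randomisation works against that. If it is applied before month 6, the primary outcome of that person is never observed. This is a conduct rule, so a separate analysis plan could not recover the missing visit.

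The rule may also not fall evenly on the two arms. Table 1 gives the control arm no self-management component at the individual, family or community level. The intervention arm has lifestyle documentation, live classes twice a week and weekly one-to-one contact, so there is more in that arm with which to fail to comply. If people who disengage are also less likely to improve, and more of them are removed from the intervention arm, imputation from those who remain would raise that arm's favourable rate.

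**Working it through.** **1. The passages side by side.** Data analysis promises analysis of all participants as randomised. The consent section allows removal from the study for non-compliance. The per-protocol sensitivity analysis makes sense only if people below its session threshold otherwise stay in the main analysis. So the analysis sections assume that non-compliers are kept, while the consent section allows them to be let go.

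**2. The plan's own figure.** Inputs from Sample size: control rate 0.02, intervention rate 0.12, power 0.80, alpha 0.05 (taken as two-sided, which the text does not state), mean rate 0.07.

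n = [1.960·√(2·0.07·0.93) + 0.842·√(0.02·0.98 + 0.12·0.88)]² / 0.10² = (0.7072 + 0.2978)² / 0.01 ≈ 101.0, rounded up to 102 per group. With 20% attrition, 102 / 0.80 = 127.5, so 128 per group. Both stated figures are reproduced. The attrition allowance is 128 − 102 = 26 people per group.

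**3. Illustration of the bias.** Assumptions, none of them given by the documents: a share f of the intervention arm is removed and nobody from control; those removed have favourable rate q; the true overall rates remain 0.12 and 0.02 (risk ratio, RR, 6.0); and imputation reproduces the rate among those retained.

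Apparent intervention rate = (0.12 − f·q) / (1 − f), and RR = that rate / 0.02.

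| f | q = 2% | q = 6% | q = 12% |
|---|---|---|---|
| 5% | 12.5%, RR 6.26 | 12.3%, RR 6.16 | 12.0%, RR 6.00 |
| 10% | 13.1%, RR 6.56 | 12.7%, RR 6.33 | 12.0%, RR 6.00 |
| 20% | 14.5%, RR 7.25 | 13.5%, RR 6.75 | 12.0%, RR 6.00 |
| 30% | 16.3%, RR 8.14 | 14.6%, RR 7.29 | 12.0%, RR 6.00 |

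For example, with f = 0.20 and q = 0.02: (0.12 − 0.004) / 0.80 = 0.145, and 0.145 / 0.02 = 7.25.

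**4. No true effect.** With 2% in both arms and only never-favourable people removed from the intervention arm, the apparent rate is 0.02 / (1 − f): 2.2% (RR 1.11) at f = 10% and 2.5% (RR 1.25) at f = 20%. The same removal in both arms gives RR 1.0.

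**5. Opposite direction.** If only control non-responders are removed, the control rate becomes 0.02 / (1 − f). A true RR of 6.0 then appears as 0.12 / 0.0222 = 5.4 at 10% and 0.12 / 0.025 = 4.8 at 20%.

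**6. The planned reference-based imputation.** Rate = (1 − f) × retained rate + f × 0.02. At f = 20%:

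- q = 2%: 0.8·0.145 + 0.004 = 0.120, RR 6.0
- q = 6%: 0.8·0.135 + 0.004 = 0.112, RR 5.6
- q = 12%: 0.8·0.12 + 0.004 = 0.100, RR 5.0

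In this illustration it is neutral or conservative.

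**7. Attrition.** Removing 20% of 128 is 25.6 people, which would use up the whole allowance of 26 before any ordinary dropout.

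**The case against.** The protocol has real safeguards. Participants are analysed by randomised group, and multiple imputation applies to all main analyses, so a removed person is not dropped from the comparison. Reference-based imputation shows that informative dropout was anticipated, and step 6 shows that it would remove the upward bias. The imputation can also draw on baseline and 3-month data, so equating it with the retained-participant average may overstate the shift. Removal is optional, study plan is not defined as adherence to the intervention, and documentation is described as voluntary. Quality control and quality assurance uses the adherence diary to strengthen the intervention, not to exclude people. The control arm also has sessions and assessments to attend.

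All of this stands, and it rules out several stronger readings that a reader might infer:

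- *That the ITT analysis is defeated.* It is not; observed outcomes are replaced by imputed ones.
- *That the effect is certainly biased towards the intervention.* Direction and size depend on removals by arm and on the outcomes of those removed, which the documents do not give.
- *That unblinded staff decide on removal.* Blinding says that those delivering the intervention cannot be blinded, but no section says that they decide on termination.
- *That a serious adverse event or new disease means leaving the study.* The disease criterion is worded around continuing the interventions, and the adverse-event criterion is limited to the intervention phase. Both can be read as stopping the intervention only; the list does not settle it.
- *That outliers are dropped.* Quality control and quality assurance says "Any data identified as unqualified will be excluded from final analysis", but this concerns data values, outliers are checked on the day of collection, and the text does not call them unqualified. It adds little here.

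The safeguards do not close the gap. The consent section names the study, no section keeps terminated people in follow-up, and the reference-based analysis is secondary and framed for people who dropped out, without saying whether that includes those removed by the investigator.

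**Conclusion.** The point holds as a weakness in the conduct rules. The protocol permits removal from the study for non-compliance after randomisation and does not provide for the 6-month assessment of anyone terminated. For those people the primary outcome would be imputed, although it could have been observed.

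A bias in favour of the intervention is plausible because that arm has more to comply with, but it is not established. An apparent RR of about 6.6 or 7.25 against a true 6.0 rests on 10% or 20% removal, in the intervention arm only, with removed people at the 2% control rate and imputation that carries no information on adherence. Under other assumptions the bias is smaller, zero or reversed. With no true effect, the shift in the illustration is 0.2 to 0.5 percentage points. The change is worth making because it is cheap and missed visits cannot be recovered later.

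**What to change.** - In Termination criteria and in the consent section, separate stopping the intervention from ending follow-up, and reconcile both with the ITT statement in Data analysis.
- Remove non-compliance as a reason to end outcome assessment.
- State that all randomised participants are invited to the scheduled assessments, at minimum the 6-month visit, and are analysed as randomised unless they withdraw consent to data collection.
- Report terminations by arm and by reason.
- State that the reference-based imputation also covers participants terminated by the investigator.

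Whether and when the intervention itself stops, including after an injury, a serious adverse event or a new disease, is a clinical decision and is not addressed here.

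The cost is protocol wording. The visits are already in the data collection schedule, and Data monitoring already provides for communicating important modifications to the parties concerned.
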